## **LIST OF ABBREVIATIONS AND RELEVANT DEFINITIONS**

|                |                                                                                                                                                                                                                                                                                                                                                  |
|----------------|--------------------------------------------------------------------------------------------------------------------------------------------------------------------------------------------------------------------------------------------------------------------------------------------------------------------------------------------------|
| ABR     | General Assessment and Registration form (ABR form), the application form that is required for submission to the accredited Ethics Committee; in Dutch: Algemeen Beoordelings- en Registratieformulier (ABR-formulier)                                                                                                                    |
| AE      | Adverse Event                                                                                                                                                                                                                                                                                                                             |
| AR      | Adverse Reaction                                                                                                                                                                                                                                                                                                                          |
| CA      | Competent Authority                                                                                                                                                                                                                                                                                                                       |
| CCMO    | Central Committee on Research Involving Human Subjects; in Dutch: Centrale Commissie Mensgebonden Onderzoek                                                                                                                                                                                                                               |
| CV      | Curriculum Vitae                                                                                                                                                                                                                                                                                                                          |
| CPPV    | Contralateral patent processus vaginalis                                                                                                                                                                                                                                                                                                  |
| DSMB    | Data Safety Monitoring Board                                                                                                                                                                                                                                                                                                              |
| EU      | European Union                                                                                                                                                                                                                                                                                                                            |
| EudraCT | European drug regulatory affairs Clinical Trials                                                                                                                                                                                                                                                                                          |
| GCP     | Good Clinical Practice                                                                                                                                                                                                                                                                                                                    |
| GDPR    | General Data Protection Regulation; in Dutch: Algemene Verordening Gegevensbescherming (AVG)                                                                                                                                                                                                                                              |
| IB      | Investigator's Brochure                                                                                                                                                                                                                                                                                                                   |
| IC      | Informed Consent                                                                                                                                                                                                                                                                                                                          |
| IMP     | Investigational Medicinal Product                                                                                                                                                                                                                                                                                                         |
| IMPD    | Investigational Medicinal Product Dossier                                                                                                                                                                                                                                                                                                 |
| MCIH    | Metachronous contralateral inguinal hernia                                                                                                                                                                                                                                                                                                |
| METC    | Medical research ethics committee (MREC); in Dutch: medisch-ethische toetsingscommissie (METC)                                                                                                                                                                                                                                            |
| PIRS    | Percutaneous Internal Ring Suturing                                                                                                                                                                                                                                                                                                       |
| (S)AE   | (Serious) Adverse Event                                                                                                                                                                                                                                                                                                                   |
| SPC     | Summary of Product Characteristics; in Dutch: officiële productinformatie IB1-tekst                                                                                                                                                                                                                                                       |
| Sponsor | The sponsor is the party that commissions the organisation or performance of the research, for example a pharmaceutical company, academic hospital, scientific organisation or investigator. A party that provides funding for a study but does not commission it is not regarded as the sponsor, but referred to as a subsidising party. |
| SUSAR   | Suspected Unexpected Serious Adverse Reaction                                                                                                                                                                                                                                                                                             |
| UAVG    | Dutch Act on Implementation of the General Data Protection Regulation; in Dutch: Uitvoeringswet AVG                                                                                                                                                                                                                                       |

**WMO**      **Medical Research Involving Human Subjects Act; in Dutch: Wet Medisch-wetenschappelijk Onderzoek met Mensen**

## SUMMARY

**Rationale:** Paediatric inguinal hernia repair is one of the most frequently performed operations in children, with an incidence ranging from 0.8 to 5% that increases to more than 30% in preterm born infants[1, 2]. Treatment is necessary because of the risk of incarceration of bowel, testis or ovary, which occurs in approximately 3-16% of children with inguinal hernia[2, 3]. Open inguinal hernia repair is the most performed treatment strategy in children, however, laparoscopic inguinal hernia repair in children is increasingly performed as it allows easy contralateral inspection and potentially results in shorter operation time and fewer complications. Nowadays, there are many laparoscopic techniques of which, in our opinion, the Percutaneous Internal Ring Suturing (PIRS) technique is the most preferable. The PIRS technique is the least invasive laparoscopic technique that uses extra-corporeal suturing and has a similar complication rate to other laparoscopic techniques. High-level evidence regarding the superiority of PIRS technique versus open hernia repair is lacking in children.

**Objective:** To study the effectiveness and a cost-effectiveness analysis of laparoscopic PIRS technique compared to open hernia repair in infants aged 0 months to 16 years of age with a primary unilateral inguinal hernia

**Study design:** A randomized controlled trial. Infants that need to undergo inguinal hernia repair will be randomized to either open or laparoscopic correction.

**Study population:** Infants aged between 0 months and 16 years who will undergo hernia repair of a primary unilateral hernia.

**Intervention (if applicable):** Open hernia repair or laparoscopic Percutaneous Internal Ring Suturing (PIRS) repair

**Main study parameters/endpoints:** Primary endpoint: Number of operations related to inguinal hernia within one year after inguinal hernia repair. Other endpoints: Duration of surgery, operative and postoperative complications, duration of hospital admission, postoperative pain, time to full recovery, CPPV-rate, cosmetic appearance and cost-effectiveness (health care and social costs). **Nature and extent of the burden and risks associated with participation, benefit and group relatedness:** Both the open and PIRS technique are commonly used techniques in paediatric inguinal hernia repair and are dependent of the surgeon performing the procedure. Therefore, no extra burden of risk exist regarding this study.

Both treatment strategies are currently performed in children with unilateral sainguinal hernia who need to undergo hernia repair. Consequently, there are no additional risks for subjects of this study and it is therefore not necessary to install a DSMB.

## 1. INTRODUCTION AND RATIONALE

The incidence of paediatric inguinal hernia ranges from 0.8 to 5% and increases to more than 30% in preterm born infants (1, 2). Treatment is necessary because of the risk of incarceration of bowel, testis or ovary, which occurs in approximately 3-16% of children with inguinal hernia (2, 3). Open inguinal hernia repair is the most performed treatment strategy in children; however, the laparoscopic approach is increasingly used in current practice (4). Although inguinal hernia repair is the most commonly performed operation by paediatric surgeons, there still is no clear consensus which technique is superior in children who need to undergo inguinal hernia repair: open or laparoscopic hernia repair.

Laparoscopic hernia repair allows better visualization of the inguinal region thereby enabling detection of a contralateral patent processus vaginalis (CPPV), which can be simultaneously closed since the presence of a CPPV might result in development of a metachronous contralateral inguinal hernia (MCIH). Open hernia repair offers the possibility for loco regional (caudal) anaesthesia, which might be beneficial as repeated or prolonged (more than three hours) general anaesthesia carries risks for near critical incidents and the U.S. Food and Drug Administration (FDA) recently released a warning that repeated or prolonged (more than three hours) general anaesthesia potentially harms the child's developmental brain(5, 6).

Over the past twenty years multiple laparoscopic techniques were developed, broadly categorized in intra- or extracorporeal techniques. These techniques varied in number of trocars, type of suturing and type of suturing materials. We recently performed a meta-analysis including all currently available randomized controlled trials comparing open and laparoscopic hernia repair (7). This meta-analysis consisted of eight trials (n=733) of which 5 compared open with laparoscopic intra-corporeal suturing and 3 that compared open with laparoscopic extra-corporeal suturing. The results of our meta-analysis showed that there were no differences when comparing the open and laparoscopic intra-corporeal suturing technique. However, subgroup analysis showed that the extra-corporeal technique resulted in less complications and a shorter operative time compared to the open technique (7).

Percutaneous Internal Ring Suturing (PIRS) technique is the least invasive laparoscopic technique that uses extra-corporeal suturing and has a similar complication rate to other laparoscopic techniques. Therefore, PIRS is the most preferable technique. The PIRS technique requires only one umbilical port and a puncture point access through were the suture is placed. In contrary to intra-corporeal laparoscopic techniques, the PIRS technique does not require intra-abdominal suturing, which is time consuming, has a high learning curve and carries a higher risk for iatrogenic visceral injury following the many manipulations with instruments in the peritoneal cavity (8, 9). In conclusion, the PIRS technique leads to visualization of the peritoneal cavity without leaving any scars and is a safe laparoscopic

hernia repair technique, even if it is performed by a surgeon with a basic skill level in endoscopic surgery (8, 10).

Several randomized controlled trials comparing laparoscopic with open paediatric hernia repair have been published, but many outcome parameters have not been addressed which include among others some peri- and post-operative complications (such as apnea, ileus) and health care costs (11). Furthermore, there is no current randomized controlled trial comparing open and laparoscopic PIRS technique. Consequently, there is an ongoing debate about the best treatment strategy and decisive evidence on the superiority of one of either treatment strategies is lacking. The aim of this randomized controlled trial is to provide an extensive comparison for effectiveness and a cost-effectiveness analysis of laparoscopic PIRS technique compared to open hernia repair in infants aged 0 months to 16 years of age with a primary inguinal hernia.

## **2. OBJECTIVES**

This randomized controlled trial studies the difference between open and laparoscopic PIRS repair with total of operations related to inguinal hernia within one year after inguinal hernia repair as primary outcome measure. Other endpoints are duration of surgery, operative and postoperative complications, use of different anaesthetic techniques, duration of hospital admission, postoperative pain, time to full recovery, CPPV-rate, cosmetic appearance and cost-effectiveness (health care and social costs).

### **3. STUDY DESIGN**

A randomized controlled trial will be performed and 464 infants with a primary unilateral inguinal hernia will be randomized to either open repair or laparoscopic PIRS repair. All operations will be performed by experienced (laparoscopic) paediatric surgeons.

One and two years after surgery all children will be called by the researcher. Prior to this call, patients or their parents will be asked to send a photo of the subject groins.. The latter is done to score testicular atrophy, recurrence or contralateral hernia. This will also be scored during a video call two years post-surgery. It is not possible to blind children or their parents/caretakers or health care professionals for the study arm, since different scars will develop and instructions have to be given for the postoperative treatment of the wound(s).

## **4. STUDY POPULATION**

### **4.1 Population (base)**

Children aged 0 months to 16 years of age with a primary inguinal hernia will be identified at the outpatient clinic by a (fellow) paediatric surgeon. Parents/caretakers will be asked to participate in this study by the (fellow) surgeon who will also ask informed consent.

### **4.2 Inclusion criteria**

In order to be eligible to participate in this study, a subject must meet all of the following criteria: infants aged 0 months to 16 years of age with a primary unilateral inguinal hernia, undergoing hernia repair.

### **4.3 Exclusion criteria**

A potential subject who meets any of the following criteria will be excluded from participation in this study: Children with 1. incarcerated inguinal hernia, which have to be operated immediately, 2. recurrent hernia 3. ventricular-peritoneal drain, 4. non-descended testis, 5. parents who are not able to understand the nature or consequences of the study.

### **4.4 Sample size calculation**

Reoperation includes both MCIH and recurrence rates. Since recent studies showed that the recurrence rate is similar between the open and laparoscopic group (0.3 vs 0.2% (12)), we used reoperation rates due to MCIH to calculate our sample size. The latest IPEG guidelines states that the MCIH rate after open repair is 6-8%. We expect that the laparoscopic repair reduces the MCIH rate to 1% since the CPPV will be closed during the same procedure. Thus, re-operation based on MCIH is performed in approximately 6% patients in the open group and in approximately 1% in the laparoscopic PIRS group. We consider a reduction of 5% of children requiring reoperation clinically relevant.

A total sample size of 422 patients is needed to detect such a reduction with a power of 0.80 at a two-sided alpha of 0.05 (nQuery Advisor 7.0). Taking into account 10% loss to follow-up we need to include 464 children. Since approximately 800-850 paediatric patients a year undergo inguinal hernia repair in our participating centres, we expect to reach our sample size within one to two years after the start of the trial. After one year of follow-up, we will perform an interim analysis to assess the effect of both treatment strategies.

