## 8. METHODS

### 8.1 Study parameters/endpoints

#### 8.1.1 Main study parameter/endpoint

Number of infants with an ipsilateral recurrent hernia or MCIH after operative repair requiring a reoperation within one year after primary surgery.

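### The allowance for 10% loss is computed as 422 × 1.10, so 464 children leave about 418 evaluable rather than 422; the period behind the 6% and 1% rates should also be stated

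*Protocol*

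**What the plan says.** Protocol section 4.4 sizes the trial on reoperation for metachronous contralateral inguinal hernia (MCIH).

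- **Rates.** The open-arm rate comes from a guideline: "The latest IPEG guidelines states that the MCIH rate after open repair is 6-8"%. The planning values are "re-operation based on MCIH is performed in approximately 6% patients in the open group" and "approximately 1% in the laparoscopic PIRS group". No follow-up period is attached to any of these figures.
- **Evaluable number.** The section gives 422 children in total, "needed to detect such a reduction with a power of 0.80" "at a two-sided alpha of 0.05 (nQuery Advisor 7.0").
- **Loss.** "Taking into account 10% loss to follow-up we need to include 464 children".
- **Recurrence.** The section says that reoperation covers MCIH and recurrence, and that sizing uses MCIH alone because recurrence is similar in the two arms (0.3% against 0.2%).

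The primary endpoint in section 8.1.1 counts infants with an "ipsilateral recurrent hernia or MCIH after operative repair requiring a reoperation within one year" of primary surgery. Section 10.1 tests it with a chi-square test. Section 8.5 says that withdrawn patients are not replaced.

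Section 3 plans later contact: "One and two years after surgery all children will be called by the researcher". Recurrence and contralateral hernia are among the things scored, again at two years. In section 8.1, every outcome that has a follow-up window ends at one year or earlier.

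**The concern.** The allowance for loss does not do what the sentence says. If 10% are lost from 464, the number remaining is below the number that the same paragraph calls necessary, and section 8.5 rules out replacement. The recruitment target rests on this figure, so it should be right even though the error is small.

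A second matter lies in the same paragraph. The 80% power is claimed for an endpoint that closes at one year, but the rates that produce it are not tied to one year. If the 6% and 1% include contralateral hernias that appear later, fewer events fall inside the endpoint window and the one-year comparison is weaker than stated. A reader of section 4.4 cannot tell whether this is so.

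**Working it through.** **Inputs (Protocol sections 4.4 and 8.2):** p1 = 0.06 (open), p2 = 0.01 (PIRS), two-sided alpha 0.05 (z = 1.960), power 0.80 (z = 0.842), 1:1 allocation, 10% loss.

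**Step 1: reproduce 422.** Pooled-variance formula for two proportions without continuity correction, with p̄ = 0.035:

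n per arm = [1.960 × √(2p̄(1−p̄)) + 0.842 × √(p1(1−p1) + p2(1−p2))]² / (p1−p2)²

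= [1.960 × 0.2599 + 0.842 × 0.2575]² / 0.05² = 210.9, so 211 per arm and 422 in total. The plan's figure is reproduced exactly.

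**Step 2: the allowance for loss.**

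- 422 × 1.10 = 464.2, which is where 464 comes from.
- 464 × 0.90 = 417.6, about 418 evaluable and 4 short of 422.
- 422 / 0.90 = 468.9, so 469 would be needed for 10% loss.
- (464 − 422) / 464 = 9.05%, so 464 covers about 9% loss; 464 × 0.91 = 422.

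**Step 3: what this costs.** The same formula solved for power at 209 per arm gives Φ[(0.05 × √209 − 1.960 × 0.2599) / 0.2575] = Φ(0.829) = 79.6%, against 80.0% at 211 per arm.

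**Step 4: recurrence.** If the plan's recurrence rates simply add to the MCIH rates (an assumption), the composite is 6.3% against 1.2%. The formula gives 216.7 per arm, 434 evaluable in total, and 78.6% power at 418.

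**Step 5: exact check of the planned test.** Enumerating all outcomes at 209 per arm, the uncorrected chi-square test has power 84.5% for 6% against 1%, and 83.1% for 6.3% against 1.2%. The planning formula is thus somewhat pessimistic for that test.

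**Step 6: sensitivity to the time horizon.** The documents give no one-year rate, so this is a range of assumptions. Planning-formula power at 418 evaluable:

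| Assumption | Open | PIRS | Power |
|---|---|---|---|
| Stated rates all fall within one year | 6% | 1% | 79.6% |
| 75% of events in both arms within one year | 4.5% | 0.75% | 67% |
| Upper end of the guideline range, all within one year | 8% | 1% | 93% |
| Upper end of the range, 75% of events in both arms within one year | 6% | 0.75% | 85% |

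**The case against.** The strongest reply is that nothing of consequence follows. The shortfall is five children on the enrolment target and 0.4 points of planning power, and the planned chi-square test still exceeds 80% by exact enumeration with 418 evaluable. That stands. It limits the point to a correction of wording, but it does not make the sentence about 10% loss true.

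Three stronger readings are tempting, and the documents do not support them.

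- **That the size is wrong for the composite endpoint.** Section 4.4 openly says that recurrence is left out and why, and including it changes little (434 against 422 evaluable; 78.6% at 418). This is a note, not an error.
- **That the trial is underpowered at one year.** The protocol does not say that the 6–8% or the 1% covers more than a year. It also takes the low end of the guideline range, which is the cautious choice. The 75% fraction in the working is an assumption with no source in the documents, and the higher open rates in the table point the other way.
- **That the two-year data are collected and wasted.** Section 3 gives a purpose for the later contacts, and an analysis plan that is not at hand may say how the data are used. What can be said is narrower: section 8.1 defines no two-year outcome.

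**Conclusion.** The point holds in a limited form. The 464 results from multiplying by 1.10 where dividing by 0.90 was needed, so it provides for about 9% loss rather than the stated 10%. The effect on planning power is 0.4 points, given the protocol's own rates, alpha and 1:1 allocation.

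The follow-up period of the 6% and 1% is not stated, and this is the only part that could move power materially. It is an omission to fill, not a demonstrated shortfall: its direction and size depend on a one-year rate that the documents do not give.

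**What to change.** In Protocol section 4.4:

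1. Correct the loss statement. Either say that 464 children allow for about 9% loss to follow-up, or say that 10% loss would require 469 and that 464 gives about 79.6% planning power.
2. Add one sentence saying that 6% and 1% are assumed to be reoperation rates within one year of primary surgery, with the source or reasoning for each.
3. If wished, note that adding the quoted recurrence rates (6.3% against 1.2%, if the rates add) gives about 78.6% at 418 evaluable.

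These are changes of wording. They need no further children or contacts; the only cost is that the stated power may read slightly below 80%.

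Optionally, define in section 8.1.2 a secondary outcome of reoperation for recurrence or MCIH within two years, using the contact already planned. This would show how many events fall after year one, but it would not alter the one-year sizing. The downside is one more secondary analysis and more missing data at two years.
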